### Recruitment of patients

Each participating practice will be asked to search their practice database using a standard electronic search provided by the research team to identify potentially eligible patients who have three or more chronic conditions as defined by the inclusion criteria. In some practices, not all GPs will participate, so in practices which have a policy for patients to see the same GP, only those patients who usually see one of the participating GPs will be included. This is to minimise the potential distress of asking a patient to change their GP for the purpose of the study. If there are more than 150 eligible patients, a simple random sample of 150 of these patients will be selected. GPs will be asked to review the resulting list to screen out patients meeting the exclusion criteria. The practice will send the remaining patients a patient invitation pack including information about the study (see online supplementary appendix 1), a consent form (see online supplementary appendix 2) and baseline questionnaire. Non-respondents will be sent one postal reminder, supplemented by a telephone reminder when possible in practices where recruitment targets are not met.

10.1136/bmjopen-2016-011261.supp1Supplementary data

10.1136/bmjopen-2016-011261.supp2Supplementary data

At sites in England, if a patient lacks capacity to consent, we will obtain the assent of the patient's carer, legal guardian or consultee on behalf of the patient to take part in the study. Carers will be invited to complete a separate carer contact form, and those who wish to participate in the carer's substudy will be sent an information sheet, consent form and baseline questionnaire.

Recruitment of patients began on 20 May 2015 and ended in December 2015. Intervention training began in June 2015 with intervention delivery period starting in August 2015 and due to finish in March 2017.

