#### Components at practice level relating to organisation of care

The aim is to identify a group of patients with high levels of multimorbidity and on several QOF disease registers in order to prioritise them for a different form of care, recognising that they have more complex needs than most patients. Consenting patients with multimorbidity (as defined in box 1) will be identified and ‘flagged’ on practice computer systems. They will be allocated a named GP with responsibility for their care (and nurse if possible, particularly in larger practices where several nurses are involved in chronic disease management). These patients will be provided with a ‘3D’ card in order to identify themselves with practice receptionists when booking appointments. The 3D card reminds the patient of their named responsible GP, and encourages them to ask for a longer appointment than usual when they think they need one. This recognises that these patients often need to discuss several problems at one appointment.

In most general practices in the UK, patients with one of the chronic conditions listed in box 1 are invited for review of that condition on a regular basis, such as every 6 or 12 months. At these reviews, the GP or nurse follow computerised disease management templates to collect relevant data about aspects of disease control and management. Patients with multimorbidity may be repeatedly called for separate reviews of each of their chronic conditions, often to see different health professionals, who use different disease management templates which include a large amount of duplication (eg, most templates include measurement of blood pressure and asking about smoking habits). Under the 3D approach, these separate disease-focused reviews will be replaced by a 3D review every 6 months at which all problems will be reviewed at one time.

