### Sample size

The study is designed to detect an effect size of 0.274 SDs in the primary outcome of the EQ-5D-5L. Data about the variability of the new five-level (5L) version of the EQ-5D is currently more limited than for the well-established three-level (3L) version. The SD of the EQ-5D-3L in the UK general population is 0.23, rising to 0.27 in the oldest respondents (aged over 75).^44^ Hence, an effect size of 0.274 would equate to a detectable difference of (0.274×0.27)=0.074 on the EQ-5D-3L, previously deemed to be the minimum important difference.^45^ Although there are less data about the variability in the 5L version of the EQ-5D than the 3L version, this latest version is likely to have greater sensitivity to change.^31^

Based on data available from our previous studies,^1^ we estimated that 2.3% of adult patients would have multimorbidity as defined in this study. This equates to about 108 patients in an average-sized practice of 6000 patients. Recruiting 32 practices would therefore provide 3456 potentially eligible patients. Assuming 40% of patients agree to participate (n=1382), 80% are followed up to 12 months, and an intraclass correlation coefficient (ICC) of 0.03 for clustering at the practice level (based on the WISE trial),^46^ 32 practices will provide approximately 90% power, with a 5% α level to detect an effect size of 0.274 SDs in the EQ-5D-5L measure between the intervention and control groups.

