### Statistical methods

Data will be analysed in accordance with CONSORT principles and its extension for cluster randomised trials. Descriptive statistics will be used to summarise characteristics of practices and patients and compare baseline characteristics between groups. A full statistical analysis plan will be developed and agreed by the Data Monitoring Committee (DMC) and the Trial Steering Committee (TSC) after completion of the pilot phase and prior to undertaking any analyses of the main trial.

All analyses of primary and secondary outcomes will be at the patient level and will account for clustering by practice using multilevel regression models. Analyses will be performed on an ‘as allocated’ basis. Primary analysis comparing EQ-5D-5L between the intervention and control practices will employ a linear multilevel regression model adjusted for stratification/minimisation variables. Subsequent models will adjust for baseline EQ-5D-5L, any variables demonstrating imbalance at baseline and other important prognostic variables such as age, number of long-term conditions, deprivation and depression. Preplanned analyses of secondary outcomes will also employ linear or logistic (as appropriate) multilevel regression models.

Formal tests of interaction will be performed to consider the following potential effect modifiers: age, number of chronic conditions, index of deprivation, and presence or absence of depression alongside physical health problems. The trial is not specifically powered for such interaction tests; hence, interpretation will focus on the CIs and will be hypothesis-generating only. The potential impact of missing data will be examined through sensitivity analyses.

Anonymised data will be used in order to compare descriptive data for consenting versus non-consenting patients. We will explore the possibility of comparing QOF performance in patients with chronic conditions both with and without multimorbidity—this is to assess for the potential unintended consequence that concentrating effort on patients with multimorbidity may have a positive or negative impact on the care of other patients.

No interim analyses are planned.

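### The exploratory QOF check groups patients by multimorbidity rather than by trial participation, so it cannot isolate spill-over in multimorbid patients outside the trial

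*Protocol article*

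**What the plan says.** The check appears in Statistical methods. It is tentative: "We will explore the possibility of comparing QOF performance". The grouping is given as "comparing QOF performance in patients with chronic conditions both with and without multimorbidity". The stated aim is to learn whether "concentrating effort on patients with multimorbidity may have a positive or negative impact on the care of other patients".

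Three other sections bear on who receives that effort:

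- Components at practice level relating to organisation of care: "Consenting patients with multimorbidity (as defined in box 1) will be identified and ‘flagged’ on practice computer systems". The named GP, the 3D card and the 3D reviews follow from that flag.
- Sample size: "Recruiting 32 practices would therefore provide 3456 potentially eligible patients", followed by the planning assumption "Assuming 40% of patients agree to participate (n=1382").
- Recruitment of patients: "If there are more than 150 eligible patients, a simple random sample of 150 of these patients will be selected". In practices where patients keep to one GP, patients of non-participating GPs are also left out, and GPs screen the list before invitations go out.

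Statistical methods also plans to compare consenting and non-consenting patients using anonymised data. That comparison is of descriptive data and is not linked to QOF performance or to trial arm.

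**The concern.** The aim concerns patients who do not get the concentrated effort. The grouping serves that aim fully only if having multimorbidity and getting 3D coincide, and by design they do not. Multimorbid patients in an intervention practice who declined, were screened out, were not sampled or see a non-participating GP remain on usual care. For this question they are other patients, and they use the same nurses and GPs for chronic disease review.

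Spill-over could go either way. Each 3D review needs a nurse appointment of 30–40 minutes and a GP appointment of 20 minutes, and practices are paid £60 for each patient who completes both six-monthly reviews, which could draw capacity away from others. Equally, merging separate disease reviews could free time, and trained staff might apply the approach more widely. The stated grouping isolates neither effect in multimorbid non-participants. An unremarkable result in the multimorbid group could therefore be read as reassurance about patients whom it does not examine separately.

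**Working it through.** **Inputs from Sample size.** 32 practices; 108 eligible patients per average practice; 40% participation. Allocation is 1:1 by practice (Allocation section). I take multimorbidity in the QOF check to mean the Box 1 definition, since no other is given.

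**The plan's own figures**
- Eligible: 32 × 108 = 3456, as stated.
- Participants: 0.40 × 3456 = 1382.4, matching the stated 1382.

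**Multimorbid patients outside the trial**
- All practices: 3456 − 1382 = 2074, and 2074 / 3456 = 60.0%.
- Per average practice: 108 × 0.40 = 43.2 participants and 108 × 0.60 = 64.8 non-participants.
- Intervention arm (16 practices): 16 × 108 = 1728 eligible, of whom 0.40 × 1728 ≈ 691 are participants and about 1037 are not.

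Where the 150 cap or the participating-GP rule applies, some multimorbid patients are never invited, so the share outside the trial can exceed 60%.

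**What the pooled group shows.** Let p be the participation share, D_P the between-arm difference in QOF achievement among participants, and D_N the difference among multimorbid non-participants. If every patient counts equally and p is the same in both arms:

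D_with = p × D_P + (1 − p) × D_N

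Setting D_with = 0 with D_P = g gives D_N = −g × p / (1 − p).

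| Participation p | Loss in non-participants that cancels a gain g |
|---|---|
| 30% (assumed) | 0.30 / 0.70 = 0.43g |
| 40% (planned) | 0.40 / 0.60 = 0.67g |
| 50% (assumed) | 0.50 / 0.50 = 1.0g |

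For illustration only, with assumed effects at 40%: +6 points in participants and −4 in non-participants give 0.4 × 6 − 0.6 × 4 = 0.

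**The other reading of the grouping.** If the multimorbid group means trial participants only, there is no pooling, but multimorbid non-participants then belong to neither group and are not examined. That reading would also largely repeat the QOF composite already listed for participants in Box 2.

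**The group without multimorbidity.** Eligibility requires three or more Box 1 condition groups, so this group contains no 3D recipients. Its between-arm comparison is not affected by the mixing.

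**The case against.** The strongest reply has four parts.

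*The check is tentative, and a full analysis plan is to follow.* True: no model or decision rule is set, and the unseen plan may subdivide further. That keeps the severity low. The point concerns a grouping that the article does state, set against a purpose that it also states.

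*The natural meaning of other patients is those without multimorbidity, and the check covers them.* This stands in large part. A reader might infer that the comparison cannot answer its own question at all. The article does not support that, because the group without multimorbidity holds no recipients and can show benefit or harm. What is left is a blind spot for one subgroup.

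*Harm would not be hidden, because participants' QOF achievement is a secondary outcome.* Partly right. With the participant difference known, D_N = (D_with − p × D_P) / (1 − p); in the illustration, (0 − 0.4 × 6) / 0.6 = −4. A reader might infer that harm would be invisible, and that goes too far. However, the subtraction needs the same measure, period and weighting in both results, which the article does not promise, and the multimorbid non-participants would still have no directly estimated difference or interval of their own.

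*Displacement is not shown.* Correct. The article gives no QOF effect for any group and itself allows for impact in either direction. Cancellation is one possibility, not a prediction.

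**Conclusion.** The point holds as a minor one. The stated grouping leaves about 60% of eligible multimorbid patients either pooled with recipients or unexamined, depending on how the multimorbid group is read. Spill-over to them, good or bad, cannot be isolated. In the pooled group, at planned participation, a gain in participants is cancelled by a loss two-thirds as large in non-participants.

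The 60% rests on the planning assumption of 40% participation and applies as an untreated share within intervention practices; nobody receives 3D in control practices. The 0.67 ratio also assumes equal weighting of patients and equal participation in the two arms. Whether any offset occurs is unknown. The primary outcome, the sample size and the listed secondary outcomes are unaffected.

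**What to change.** If the comparison goes ahead, define the groups by trial participation as well as multimorbidity, and compare QOF achievement between arms separately in:

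- (a) trial participants;
- (b) multimorbid patients not in the trial, for whatever reason;
- (c) patients with chronic conditions but without multimorbidity.

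Base the conclusion on spill-over on (b) and (c), and use the same QOF measure in all three groups. The contrast should be between arms within each group, because people who consent may differ from those who do not. The design allows this, since patients are identified and invited before their practice is randomised.

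The cost is one extra grouping in an anonymised practice extraction, with smaller groups and wider intervals. Anonymised data on non-consenting patients are already foreseen. The extraction should also cover multimorbid patients who were never invited, namely those beyond the sample of 150 and those of non-participating GPs.

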### Economic analysis

Cost per patient will be estimated by applying unit costs to the resources used. In a cost-consequences analysis, we will relate the mean cost per participant in each group with changes in a range of outcomes; cost-effectiveness analysis from the NHS and PSS perspective will estimate the incremental cost per QALY gain where QALYs are estimated using the EQ-5D-5L. Uncertainty will be addressed in sensitivity analyses and by using bootstrapping to estimate the net monetary benefit and a cost-effectiveness acceptability curve.

### Process evaluation

Alongside the main analysis of quantitative outcomes from the trial, we are conducting a nested process evaluation. This mixed-methods study aims to better understand how and why the intervention was effective or ineffective and to identify contextually relevant strategies for successful implementation as well as practice difficulties in adoption, delivery and maintenance of the intervention. Further details of the protocol for the process evaluation will be published in a separate paper.^47^

## Ethics

### Ethics approval

This study will be conducted in accordance with principles of good clinical practice.

Patients will not be denied any form of care that is currently available in the NHS by participating in this study. Patients from usual care practices will still have access to all locally recommended treatments and services. Patients from intervention practices will still have full access to their GP and secondary care services in addition to their six-monthly 3D assessments. Any changes in medication prescribing will be performed by a GP in the context of normal clinical care.

### Patient safety

We will monitor and report descriptively the numbers of serious adverse events in each arm which appeared to be related to the intervention or the trial, and also the number of deaths in each trial arm. Given that patients with multimorbidity may be heavy users of secondary care services, new medical diagnoses, hospital admissions and deaths are expected and will not be considered as potential serious adverse events unless anyone involved in the study (participants, general practice staff or research staff) notify the research team of any events that they consider may have been related to the intervention or the research process. All deaths will be investigated for relatedness by requesting the patient's GP provide details of cause of death and relatedness to study.

### Study management and oversight

The 3D Study is managed by the Trial Management Group, consisting of the chief investigator, principal investigators and researchers from each of the recruiting sites and other co-applicants. There is additional governance oversight by an independent TSC and an independent DMC, both constituted in line with guidance from the National Institute for Health Research (NIHR). An advisory group with members from key local and national stakeholder organisations and lay members has been convened to provide advice about the wider context, other related initiatives and to facilitate communication and eventual knowledge mobilisation with regard to this trial. There is an active patient and carer forum which meets regularly to advise on the design and conduct of the study.

The project will seek to maximise the impact of the research by adopting a model of knowledge transfer. We aim to disseminate our findings to patients, healthcare professionals, commissioners and other academics. In addition to publication of study results, guides for commissioners and for practices will be produced to enable wider implementation of the new 3D approach. The RCGP Clinical Innovation and Research Centre will facilitate wide dissemination to practices and the production of these resources.

The research team is committed to full publication of the results. Authorship will be in accordance with the guidance of the International Committee of Medical Journal Editors. All authors will have full access to the study data. Once the main results have been published, data may be available to other investigators subject to agreement about the protocol with the chief investigator and compliance with policies of the funder and sponsor in relation to data sharing. The study sponsor and the funder will have no role in study design, data collection, management, analysis or interpretation of data, writing of the final report or the decision to submit for publication.

## Discussion

This large and rigorous trial will provide robust evidence about the benefits and costs of a pragmatic intervention to improve the management of multimorbidity in general practice. It builds on a considerable evidence base about the difficulties experienced by patients with multimorbidity and the health professionals who seek to care for them. Through the use of a patient-centred conceptual framework, it tests a range of strategies which should address these difficulties and improve outcomes that matter to patients. The study is highly pragmatic.^48^ It is based in a range of normal general practice settings and in the different health economies of England and Scotland, which will enhance generalisability. It includes patients with broad inclusion criteria and few exclusion criteria, and assesses a wide range of outcomes including those relating to health status, patient experience and resource utilisation. Implementation of the intervention is flexible to local context, but the extent to which the intervention adheres to the key-intended principles will be monitored.

The study is being conducted with considerable attention to principles of knowledge translation. If the intervention is effective, it will be possible to roll it out quickly to general practices across the UK, and the 3D approach is also likely to be applicable to the management of patients with multimorbidity in many other countries.
